## Methods

### Aims, design and setting

The primary aim of this study is to evaluate the effectiveness of the BetaMe programme versus usual care among primary care populations in improving the control of T2DM and pre-diabetes, as measured by change in HbA1c and weight over a 12-month period.

The secondary aims, which will be explored using secondary analysis of the data, are to evaluate the effectiveness of the BetaMe programme versus usual care in:Improving HbA1c and weight outcomes at 12 months for Māori and Pacific participants specifically (combined across T2DM and pre-diabetes groups);Improving short-term weight management among those with T2DM and pre-diabetes (at 4 months, both overall and reported for Māori and Pacific participants);Improving other health-related outcomes, including waist circumference, blood pressure, health-related quality of life and self-reported self-management (overall and reported for Māori and Pacific participants)

The study will be a two-arm, parallel-group, individually randomised controlled trial for people with pre-diabetes and T2DM, comparing the BetaMe programme with usual primary care (active control), with investigator-blinded assessment of outcomes (see Fig. 1 for the flowchart of the BetaMe study, Additional file 1 for the Standard Protocol Items: Recommendations for Interventional Trials (SPIRIT) Checklist and Fig. 2 for the SPIRIT Figure).

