The study is powered in the pre-diabetes group to detect a difference of 2.5 mmol/mol between study arms (80% power, alpha = 0.05, presuming SD = 5.5 mmol/mol [42]). This requires a sample size of 76 per study arm (152 total). In the pilot study, the mean reduction in HbA1c was 2.6 mmol/mol. The sample size for the T2DM group is powered to detect a minimal clinically important difference [43, 44] of 5.5 mmol/mol between study arms (80% power, alpha for comparison = 0.05, presuming a standard deviation of 15 mmol/mol in this group [16]). This requires a sample size of 117 per study arm (234 total). This gives a combined sample size of 386 people with pre-diabetes and people with T2DM. To account for loss of precision due to patients lost to follow-up (projected at 10% [45, 46]), we will recruit 430 patients at baseline (note that all participants will be included in linear mixed models analysis, even if missing final endpoint data, which reduces bias in estimating effect size, but there is still loss in statistical power compared to having complete follow-up data).

Analysis of weight differences between study arms will use the same analytical methods as for the HbA1c outcome. For these weight analyses, those with pre-diabetes and T2DM will be pooled prior to analysis as the relevant intervention target weight loss is the same for these two groups. Analysis will be stratified on patient group to account for the pooled approach, and we will also report weight differences by study arm within each patient group. The comparison of weight loss in the combined patient group is powered to detect a difference between study arms of 5 kg (80% power, alpha = 0.05, SD = 15 kg in this group [47]). This requires a sample size of 142 per study arm (284 total), which is within the combined sample size calculated for the HbA1c outcome.

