We will also estimate differences in HbA1c and weight endpoints by study arm for each of the stratified randomisation ethnic groups (Māori, Pacific, other ethnicities), and will report the mean intervention effect and 95% confidence interval for each group. Proportions of patients meeting HbA1c and weight-loss targets will also be analysed by ethnic group with logistic regression (adjusted for baseline covariates), and adjusted absolute risk differences in treatment outcomes will be computed to quantify treatment effectiveness [48]. Assuming that 20% of the sample will be Māori (*n* = 234 × 0.2 = 46 Māori participants) gives an anticipated margin of error on the intervention effect of ± 4.5 mmol/mol for HbA1c in the diabetic group.

Analysis of self-reported outcomes will be conducted in a similar way.

Results will be actively disseminated (see Additional file 3).

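### The ±4.5 mmol/mol margin of error given for Māori participants with T2DM is about half the between-arm margin that the plan's own inputs produce (about ±8.7)

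*Protocol article*

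**What the plan says.** The protocol article, Sample size and analysis, plans to estimate the difference in HbA1c by study arm within each ethnic group used to stratify randomisation, and "will report the mean intervention effect and 95% confidence interval for each group". It then gives one precision figure. "Assuming that 20% of the sample will be Māori", and taking "234 × 0.2 = 46 Māori participants", it says that this "gives an anticipated margin of error on the intervention effect of" ± "4.5 mmol/mol for HbA1c in the diabetic group".

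The same section sizes the T2DM group for a minimal clinically important difference of 5.5 mmol/mol with 80% power and alpha 0.05, "presuming a standard deviation of 15 mmol/mol in this group". The result is 117 per arm, 234 in total. Randomisation and blinding sets 1:1 allocation, stratified by practice and ethnicity.

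**The concern.** The ±4.5 is attached to the intervention effect, which this section defines as a contrast between arms. Only about 23 of the 46 people will be in each arm, and a contrast of two small groups with SD 15 should be far less precise than that.

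Effectiveness for Māori and Pacific participants is the first-listed secondary aim, and the Discussion names it again as an explicit aim. The figure also sits on the wrong side of the plan's own benchmark. At ±4.5, an estimate near zero would appear to rule out a 5.5 mmol/mol benefit in Māori participants with T2DM. At about ±8.7 it would not. A reader relying on the printed figure could take an inconclusive subgroup result as evidence of no benefit.

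**Working it through.** **Inputs**, all from the protocol article:
- SD of HbA1c in T2DM: 15 mmol/mol (Sample size and analysis).
- Māori participants with T2DM: 234 × 0.2 = 46.8, given as 46 (same section). The 234 is the number before the 10% allowance for loss to follow-up, so 46 counts people with outcome data.
- Allocation 1:1, stratified by ethnicity (Randomisation and blinding): about 23 per arm.
- Confidence level: 95% (Sample size and analysis).

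**Step 1: confirm how the plan uses SD 15.** The two-sample formula 2 × (1.96 + 0.842)² × 15² / 5.5² gives 116.8, so 117 per arm. This is the plan's number. SD 15 was therefore used as it stands, with no reduction for baseline adjustment.

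**Step 2: try to reproduce ±4.5.**
- Single mean of 46 people: 15/√46 = 2.21. Multiplied by t(0.975, 45 df) this gives 4.45, which rounds to 4.5. With 1.96 it gives 4.33.
- Difference between arms, 23 + 23, 95%: 1.96 × 15 × √(2/23) = 8.67. With t on 44 df it is 8.91.
- Other variants: 46 per arm gives 6.13; a 90% interval with 23 per arm gives 7.28; an 80% interval gives 5.67; 77 people in total (20% of 386) at SD 15 gives 6.70.
- The between-arm standard error alone is 15 × √(2/23) = 4.42. It rounds to 4.4 and is not a 95% margin.

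Of the 95% margins tried with the stated inputs, only the single-mean margin gives 4.5.

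**Step 3: size of the discrepancy.** 8.67/4.5 = 1.93 and 8.91/4.5 = 1.98.

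**Step 4: a check that needs no guess about the formula used.** The whole T2DM group (117 per arm) has a between-arm margin of 1.96 × 15 × √(2/117) = ±3.84. One fifth of that sample should have a margin √5 times wider: 2.236 × 3.84 = ±8.6. The printed ±4.5 would mean that dropping 80% of participants widens the interval by only 17% (4.5/3.84 = 1.17).

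**Step 5: what would make ±4.5 right as a between-arm margin.**
- With SD 15: 4 × (1.96 × 15/4.5)² = about 171 Māori participants with T2DM, against 46.
- With 23 per arm: a residual SD of 4.5/(1.96 × √(2/23)) = 7.8, which corresponds to a baseline-to-outcome correlation of √(1 − (7.8/15)²), about 0.855.
- With SD 7.8, the T2DM sample size would be 2 × (1.96 + 0.842)² × 7.8²/5.5² = 31.6, so 32 per arm rather than 117. The two figures in this section cannot both follow from one set of assumptions.

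**The case against.** The strongest defence is that the planned analysis is not an unadjusted comparison. It is a mixed model adjusted for baseline HbA1c, age, gender, ethnicity and weight, and it uses the 4-month data, so the achieved margin may well be narrower than ±8.7. Eligibility also limits baseline HbA1c to 41–70 mmol/mol, so the baseline SD cannot exceed 14.5. Part of this stands: ±8.7 should be labelled unadjusted, not offered as the margin the trial will achieve. It does not rescue ±4.5. The article gives no correlation. Under assumed correlations of 0.5, 0.7 and 0.8 the margin is ±7.5, ±6.2 and ±5.2, all above 4.5. Twelve-month values are not bound by the eligibility range, and the plan itself sizes the group with SD 15.

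A second defence is that this is a remark on anticipated precision for a secondary, estimation-only analysis. The article claims no power and sets no decision rule for the subgroup, and the reported interval will show its own width. That stands, and it limits the consequence. It does not make the printed number correct.

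A reader might go further than the documents allow in three ways:
- **Treat the single-mean formula as the proven cause.** No formula is shown. The match is close, but the origin remains an inference, and the mismatch holds whatever the origin.
- **Fault the article for giving no Pacific margin and none for the aim worded as "Māori and Pacific participants specifically (combined across T2DM and pre-diabetes groups").** The ±4.5 is openly labelled as applying to the diabetic group, and leaving other margins out of a condensed article is not an error. Nor does the article fix a combined value. Its SDs give about ±5.4 with one SD pooled by group size but about ±3.6 with inverse-variance weighting, and it states no weighting for a combined HbA1c estimate.
- **Conclude that no subgroup estimate could exclude 5.5 mmol/mol.** That is too broad. The 5.5 is the T2DM difference, while the pre-diabetes group is sized for 2.5. Even at ±8.7, an estimate favouring control by more than about 3.2 (8.7 − 5.5) would exclude it.

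**Conclusion.** The point holds for the one figure printed. With the plan's SD of 15 mmol/mol, 46 people split evenly and a 95% level, the unadjusted between-arm margin for Māori participants with T2DM is about ±8.7 mmol/mol (±8.9 with t), 1.9 to 2.0 times the stated ±4.5. The correction moves the margin from below to above the plan's 5.5 mmol/mol benchmark. The result assumes equal arms, complete outcome data on the 46 and no gain from covariate adjustment. With adjustment the margin would be smaller by an amount the article gives no basis to fix, and ±4.5 would need a residual SD of about 7.8, at odds with the section's own sample size. The error is one of stated precision for a named secondary aim. The primary analyses and the total of 430 do not depend on it.

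**What to change.** In Sample size and analysis, replace ±4.5 with about ±8.7 mmol/mol and label it as the unadjusted 95% margin with SD 15 and 23 per arm. Alternatively, if a smaller residual SD after baseline adjustment was intended, state it, justify it, and explain why the T2DM sample size does not use it.

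Add one sentence saying that a near-null estimate in Māori participants with T2DM would not by itself rule out a 5.5 mmol/mol benefit.

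The cost is one number and one sentence, and a less favourable statement of precision. Recruitment, randomisation, analysis and conduct do not change.

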#### Data management

Baseline and follow-up data are entered directly by patients and research nurses at the time of the relevant assessments in to a REDCap database. Range checks are in place for relevant variables such as HbA1c levels (41–70 mmol/mol). All data are checked by research nurses at the time of their entry and those variables that are used for stratified randomisation (ethnicity, practice and HbA1c) are re-checked by the research manager prior to randomisation. Participants’ data will be de-identified by a unique code number and information linking that code to a particular patient (NHI and unique trial-specific code number) will be kept in a secure location with password protection. A master list which links the patients’ NHI and trial code number will be kept so any information about the study, including results, can be communicated to participants. Analysis will be carried out on de-identified data. All trial-specific data for the study will be securely stored by the research team for 10 years once the trial has ended.

#### Data monitoring

An independent Data Monitoring Group is not required for this study because the study is low risk in terms of likelihood of life-threatening complications or serious adverse events, the study team has no professional or financial links with the company that is delivering the intervention, and it will not be necessary to instigate stopping rules because there will be no interim analyses of efficacy [49]. An internal Data Monitoring Group will be convened at 2-monthly intervals which will consist of the study PIs (DS and MM) and the biostatistician (JS). This group will also include an independent senior researcher. This group will assess the effectiveness of study procedures, review any potential adverse events and review and approve any amendments to study protocols. Other members of the research group will provide advice and input if requested.

### Process evaluation

At the end of the study, there will be a process evaluation, which will include assessments of implementation of the BetaMe programme and mechanisms of action. Data will be collected from three sources: (1) from the mobile/web platform to identify key usage patterns; (2) with consent from the participants, health coaches will record audio interactions with participants and will log key reasons for contact (a random subset of the coaching sessions will be assessed by the research team for consistency with the log); and (3) participants will be invited to provide individual feedback on the acceptability and usefulness of the intervention at the end of the study period.

Focus groups, lasting approximately 1 h each, will be held in each region to obtain in-depth feedback about the intervention and how participants interacted with it. Usage will be described, and linked to outcomes using standard quantitative analytic approaches (for example, proportions accessing health coaches will be reported, with 95% confidence intervals; frequency of accessing health coaches or engaging online will be reported as median access with range/interquartile range). Focus group data will be coded thematically, with key issues identified.

### Trial registration

The trial is registered with the Australian New Zealand Clinical Trials Registry on 19 April 2017. Registration number: ACTRN: ACTRN12617000549325. See http://www.ANZCTR.org.au/ACTRN12617000549325.aspx. The full protocol is available at this site, including consent forms and detailed documentation. Any important protocol modifications will be reported to this organisation.

This trial’s Universal Trial Number (UTN) is U1111–1189-9094.

## Discussion

Long-term conditions pose a great burden to patients, family/whānau and health services. Self-management interventions are a potential way to address this burden with evidence that they can be effective in improving physical and mental health. Important gaps in evidence remain, and are a barrier to implementation. The BetaMe programme is an integrated, evidence-based, comprehensive, self-management programme delivered by mobile and web-based technology. A pilot of 117 patients with pre-diabetes was extremely successful with 78% of people reducing their HbA1c level below pre-diabetes range over 4 months. However, the study was volunteer-based and did not incorporate a comparison arm.

This paper describes the protocol of a study that will address the question of whether this kind of programme is likely to be effective in reducing HbA1c and weight among people with T2DM and pre-diabetes in a primary care environment. It addresses shortcomings of previous studies and includes an explicit aim to assess the effectiveness of this kind of programme among Māori and Pacific people who have higher rates of T2DM and pre-diabetes than other ethnic groups in NZ.

If found to be effective, this programme would allow healthcare providers to deliver an intervention that is person-centred and supports the self-care of people with T2DM, pre-diabetes and potentially other LTCs.

## Trial status

This paper is based on protocol version 1.2, dated 1 August 2017. Recruitment to the study began on 9 June 2017. Approximate date of recruitment completion: February 2018.

## Abbreviations

BMI: Body Mass Index
EQ-5D-5L: five-level EuroQol five dimensions questionnaire
LTC: Long-term conditions
NHI: National Health Index
NZ: New Zealand
PHO: Primary Healthcare Organisation
PI: Primary investigator
T2DM: Type 2 diabetes mellitus
